## Abstract

**Background:**

The International Classification of Functioning, Disability and Health (ICF) defines participation as a person’s performance in life situations, including the size of social networks, and satisfaction with social contacts. Stroke survivors are known to experience a reduction in the number of their social networks and contacts, which cannot be explained solely in terms of activity limitations caused by physical impairment. Problems of emotional processing, including impaired mood, emotion regulation and emotion perception, are known to occur following stroke and can detrimentally influence many aspects of social interaction and participation. The aim of this study is to investigate whether emotion processing impairments predict stroke survivors’ restricted social participation, independent of problems with activity limitation.

**Methods/design:**

We aim to recruit 125 patients admitted to NHS Grampian with a confirmed diagnosis of stroke. All participants will be assessed on measures of emotion processing, social participation and activity limitation at approximately one month post stroke and again at approximately one year post stroke in order to assess change over time.

**Discussion:**

It is important to develop a greater understanding of the emotional factors which may underlie key social deficits in stroke recovery in an ageing population where stroke is one of the leading causes of severe, complex disability. This research may enable us to identify those who are risk of participation restriction and target them in the acute stroke phase of stroke so that adverse outcome is avoided and rehabilitation potential is fulfilled.

## Background

The International Classification of Functioning, Disability and Health (ICF) [1] provides a conceptual framework for examining the consequences of a health condition in terms of function and disability and illustrates how a health condition, such as a stroke, may impact upon an individual and their life (Figure 1).

**Figure 1 F1:**
[figure not shown]
Graphic presentation of the ‘disability’ model of the International Classification of Functioning Disability and Health (World Health Organisation, 2001).

The ICF has three health components, and a health condition may cause difficulty in any of these areas: The stroke may result in *Impairment* in the body function or structure, perhaps an inability to move a leg. Limitations in the individuals’ ability to execute an activity may occur resulting in an *Activity Limitation*, e.g. they may be unable to walk. Individuals may find themselves restricted in what they can participate in, e.g. perhaps they cannot participate in a social gathering, such as attending a walking club or even walking to church and as such will experience *Participation Restrictions* from this loss of social engagement in a life situation. These three health components of the ICF are further influenced by personal and environmental factors, which are unique to the individual, such as personality and beliefs, friends and family, as well as home environment. Crucially, within the ICF, difficulties can occur in one domain and not in another, so the relationship between the components of Impairment, Activity Limitations and Participation restrictions is not necessarily causal.

This current research investigates the health condition of stroke and looks at impairment in activity limitations and participation restrictions by examining the influence of impairments in emotion processing on social participation whilst controlling for activity limitations.

This research is informed by the literature in the fields of stroke, emotion processing and participation recovery in stroke, and this study protocol details the proposed methodology and analysis plan for this research.

### Stroke

Stroke is an increasingly common condition, and is the leading cause of severe, complex disability in the UK. More than 250,000 people live with disabilities caused by stroke. Economically, stroke care consumes an in excess of £2.8 billion of the UK National Health Service money each year in direct costs [2]. Within Scotland alone stroke care accounts for 5% of the total NHS budget [3]. Recovery from stroke is often associated with an intensive period of rehabilitation, with a focus on reducing levels of impairment and activity limitations. However, several studies investigating recovery from stroke over time, including a review of qualitative studies, have suggested that stroke survivors themselves do not tend to think of their aims in terms of overcoming physical limitations [4-6], but rather focus on achieving social integration back into community, family and work life.

There are many factors influencing stroke rehabilitation and recovery, and many barriers to the fulfilment of such a goal, in part due to the wide range of functions which stroke can impair, including motor control, language, memory and emotion processing. Given the ageing of the population, it is likely that incidence of stroke will continue to rise, and with more individuals surviving stroke, this is likely to be associated with important consequences for social interaction and the quality of life of both stroke survivors and their families.

### Social participation

The World Health Organisation has defined successful rehabilitation as reintegration of the individuals back into their social networks and participation in activities and the community [7]. Level of social participation is increasingly becoming regarded as a pivotal factor in successful rehabilitation [7]. The term social participation refers to the engagement in a variety of life situations, such as hobbies, recreation time, socialising, work, as well as the number and frequency of contacts an individual has. Yet stroke survivors are known to experience a reduction in social participation, as observed in reduced engagement in leisure and social activities, which cannot be explained solely by activity limitation [8,9]. Stroke survivors are also known to experience a decline in social networks and contacts [10]. Decreases in the quantity and quality of their social participation and interactions are key factors in levels of self rated quality of life [11]. Social participation has also been shown to be a key determinant of discharge destination from hospital suggesting that factors other than motor and cognitive limitations may be important in influencing post-stroke outcomes [12].

### Emotion processing

We aim to measure emotion processing in relation to three constructs of emotional experience and emotion skills; 1) Emotion Perception, 2) Emotion Regulation, and 3) Depression and Anxiety. Emotion processing has been recognised as a crucial component in social interactions between individuals [13] and as such difficulties in emotion processing may have implications for the individual’s ability to participate and interact in social situations [13,14]. First, impairment in the ability to accurately perceive emotions may impact on social participation as this skill forms an important part of our social interactions. Inability to judge whether someone is happy, sad, or angry, may result in confusing and dissatisfying social interaction, leading to increasing withdrawal from social situations [13,15]. Second, emotion regulation, specifically, this refers to the awareness, understanding and monitoring of our own emotions so that we may evaluate and influence which emotions we experience, when we experience them and crucially how strongly we experience them, in order to produce desired emotional states and goals. Finally, anxiety and depression are known to impact on the desire to engage in social interactions and participate in activities with other people [16]. In addition to this depression is known to affect how aware and sensitive we are to other people emotions [17] and is also associated with difficulties in emotion regulation [18]. In terms of stroke survivors, there is evidence to suggest that they are prone to all of these types of emotion processing impairment.

*Emotion perception* involves the identification of emotionally-salient information in the environment, and the decoding of these emotional states. This ability to decode emotional signals from faces and voices is considered to be an important component in the generation of emotional responses, emotional experiences and successful interaction in a social environment [14,19,20].

Numerous studies have investigated emotion perception ability in stroke survivors and demonstrated impairment in this ability [19-22]. However, to date, these have focused on focal unilateral brain lesions to investigate the role of each hemisphere of the brain in emotion perception abilities and have not examined the impact of such impairments on the individual’s life experience. Furthermore, there is little data available to evaluate the role of psychological factors on emotion perception following stroke. For example, stroke frequently results in depression, and this might influence aspects of emotion perception. Research with patients with major depression have demonstrated impairments in emotion perception [19,23] and this has been considered a factor in the progress and consolidation of depression. Montagne, et al. [19] found that depressed stroke patients were significantly more impaired in labelling emotions than both the controls and non-depressed stroke patients. The results of this study suggest that mood disorders may interact with stroke to influence emotion perception. As emotion perception ability has been demonstrated to be a key factor in social interactions and communication, the relationship between mood, emotion perception and social participation warrants further investigation in stroke survivors [14].

The definition of *emotion regulation* in the current research refers to the awareness, understanding and monitoring of our own emotions so that we may evaluate and influence which emotions we experience, when we experience them and crucially how strongly we experience them, in order to produce desired emotional states and goals. Individuals utilise different emotion regulation strategies in order to effectively control their emotions, enabling them to produce the emotional state which they wish to attain. The importance of emotion regulation has been highlighted in clinical populations, where impairments in this ability are correlated with the severity of their mental health condition [18,24,25]. Depression, anxiety, post traumatic stress disorder and schizophrenia are illnesses which have all been shown to impair emotion regulation, and although no direct link has been explored, these conditions are all associated with reduced social participation. Emotion regulation has also been identified as an important factor in psychological adaptation to chronic illness [26]. Successful emotion regulation has been associated with better perceived health, including psychological well-being and social functioning [27]. Although there has been no direct link explored between emotion regulation, as defined within this research, and stroke, specific brain networks are known to be responsible for emotion regulation [28]. As in the case of emotion perception, it is therefore possible that the lesion to the brain caused by the stroke may itself result in impaired emotion regulation. It is also possible that a reactive response to the stroke, as can be the case in depression, may also result in emotion regulation impairment. Here we explore the links between emotion regulation difficulties following stroke and social participation.

*Depression and anxiety* are relatively common following a stroke. A Cochrane review of literature suggested that at least one quarter of patients will experience depressive and anxiety disorders in the first year after onset of stroke [29]. Although the relationship between depression and the consequences of stroke is a complicated one, research has suggested that abnormal mood is correlated with impairments of physical, social and cognitive function, increased mortality and contributes to stress on carers [29-33]. Depression in stroke has been correlated with reduced social participation and contacts [16]. Less is known about anxiety following stroke and its impact on social participation.

### Aims and objectives

Therefore, this research aims to explore three different facets of emotion processing following stroke, exploring which difficulties in emotion processing occur and how these impairments impact on social participation in stroke survivors, while controlling for levels of activity limitation.

Participants will complete measures twice, at approximately one month post stroke and one year thereafter. This will allow the examination of the extent to which impairments in emotion processing are associated with social participation at both acute and chronic phases of stroke recovery. Also, by assessing participants longitudinally, direction of causation between emotion processing difficulties and social participation limitations can be explored.

The specific research questions which we will address are:

1) During the acute phase, approximately one month post-stroke, are deficits in emotion processing correlated with levels of social participation?

2) During the chronic phase, approximately one year post-stroke, are deficits in emotion processing correlated with social participation?

3) do emotion processing deficits in the acute phase of stroke predict social participation at one year post stroke which is not accounted for by activity limitation?

## Methods

### Design

This is a predictive study with a prospective design. Measures of emotion processing and social participation administered at baseline will be used to predict participation outcome at one year post stroke.

### Participants

A sequential cohort of 125 patients, approximately one month post stroke, will be recruited from the rehabilitation and acute stroke units, stroke outpatient clinics, and the NHS Grampian Stroke Register within Aberdeen Royal Infirmary and Woodend Hospital, Aberdeen. Potentially eligible participants are to be identified in collaboration with the acute stroke unit lead clinician.

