### Inclusion criteria

Participants are included according to the following criteria: 1) a confirmed diagnosis of stroke, defined as the presence of symptoms persisting beyond 24 hours and/or a positive CT scan, one month previously; 2) no pre-existing neurological condition, psychiatric condition or chronic drug/alcohol abuse known to affect emotion processing; 3) no severe cognitive impairment (MMSE score >23).

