### Procedure

Consecutive recruitment will be employed with potentially eligible participants identified from the stroke units and clinics. Participants are invited to participate in the study by letter from the lead clinician. Participants on the ward are given the letter, a participant information sheet and a reply form, and may then put their reply form in a box provided at the nurse’s station on the ward if they wish to participate. Participants discharged to home receive the same letter, information sheet and reply form posted to their home with a freepost envelope to post their reply form back to the researcher if they wish to participate. Participants who consent are required to complete two sessions, each session lasting approximately one and a half to two hours. The first session is to occur at approximately one month post stroke and the second session is to occur at approximately one year post stroke. All measures are administered at both time points. Participants can opt to split each session into multiple sessions should they wish to, to ensure that participants do not become fatigued. Participants can be assessed on the ward, in their home or at the University of Aberdeen.

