### Analysis

Initially, a correlational analysis will be conducted on the measures from each domain of emotion processing to ascertain if the measures within that domain are highly correlated with each other. If this is the case the measures will be amalgamated. The same process will be conducted with the measures of social participation. Should the measures not be highly correlated an exploratory factor analysis will be conducted.

Regression analyses will be conducted to investigate whether the emotion processing measures predict social participation measures, controlling for activity limitations. The final research question was whether emotion processing deficits in the acute phase of stroke predict social participation at one year post stroke which is not accounted for by activity limitation? To address this, hierarchical regression analyses will be conducted, predicting social participation at second assessment from concurrent activity limitation in the first step and emotion processing from the acute phase of stroke entered in the next step of the regression.

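### Days since stroke at the first assessment may vary but enter no stated model; adding them is a nearly free safeguard, mainly for question 1

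*Protocol article*

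**What the plan says.** On timing, the Participants section states "A sequential cohort of 125 patients, approximately one month post stroke, will be recruited", and Procedure repeats it: "The first session is to occur at approximately one month post stroke". The Inclusion criteria date the stroke with the words "a positive CT scan, one month previously". None of these gives a tolerance in days.

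On recruitment, patients come "from the rehabilitation and acute stroke units, stroke outpatient clinics, and the NHS Grampian Stroke Register". Ward patients reply through a box on the ward. For the others, Procedure says "Participants discharged to home receive the same letter, information sheet and reply form posted to their home", with a prepaid envelope for the reply. An assessment need not fall on one day: "Participants can opt to split each session into multiple sessions should they wish to".

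On the models, the Analysis section will examine whether the "emotion processing measures predict social participation measures, controlling for activity limitations". For question 3 it fixes the order of entry: activity limitation measured at the second assessment in the first step, acute-phase emotion processing in the next. Neither days since stroke nor recruitment route is named in any model.

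**The concern.** The study measures everything at two times because it expects patients to change between the acute and chronic phases. If emotion scores, participation and activity limitation are already changing around the first visit, a patient seen later after stroke may score better on all three. Time since stroke is then a common cause of predictor and outcome in question 1, where both are measured at the same visit. Adjusting for activity limitation at that visit removes part of this, but not all.

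Question 3 differs. The outcome is taken about a year after stroke, so timing of the first visit mainly adds noise to the acute emotion score. The one-year activity limitation in step 1 cannot correct for recovery stage when that score was taken.

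The variable should already be available, because the eligibility rule cannot be applied without the stroke date. At stake is a slightly inflated error rate in question 1 and a slightly weakened predictor in question 3.

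**Working it through.** **The plan's own figure.** The Sample size section gives 119 for an F test with a medium effect, alpha 0.05 and power 0.95. Two inputs are assumed: f² = 0.15 (the usual convention for medium) and 3 tested predictors (the three emotion constructs). With the noncentral F distribution and λ = f²·N, the required N is 119 for an overall test of 3 predictors, and also 119 for the R² increase from 3 predictors over 1 covariate. The stated figure reproduces.

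**Question 1: model.** The article gives no spread of visit times, so the time effects are assumptions shown over a range. Let T be days since stroke, E emotion, A activity and P participation, all standardised and scored so that higher is better:

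- E = a·T + error
- A = a·T + error
- P = 0.5·A + d·T + error, with no effect of E

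Then r(E,A) = a², r(A,P) = 0.5 + d·a, r(T,P) = d + 0.5·a and r(E,P) = a·r(T,P). The partial correlation given activity is

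r(E,P|A) = [r(E,P) − r(E,A)·r(A,P)] / √{[1 − r(E,A)²]·[1 − r(A,P)²]}.

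The rejection rate follows from f² = r²/(1 − r²) and λ = 125·f², with F on 1 and 122 degrees of freedom.

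**Question 1: time correlates a with every score in total.** Here d = a − 0.5·a. For a = 0.3: d = 0.15, r(A,P) = 0.545, r(E,P) = 0.09, and the partial r is 0.09 × 0.455 / √(0.9919 × 0.7030) = 0.0410 / 0.835 = 0.049.

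| Total correlation with time | Partial r given activity | False-positive rate |
|---|---|---|
| 0.1 | 0.006 | about 5.0% |
| 0.2 | 0.022 | 5.7% |
| 0.3 | 0.049 | 8.5% |

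**Question 1: larger effects.** If 0.2 or 0.3 is instead the direct effect d, on top of the path through activity, the total correlation of time with participation is 0.2 + 0.5 × 0.2 = 0.30, or 0.3 + 0.5 × 0.3 = 0.45. The partial r is then 0.046 or 0.102, and the rate 8.0% or 20.6%.

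In every case, conditioning on T as well returns the partial r to 0.

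**Question 1: in days, without activity adjustment.** Suppose both scores improve by 0.01 to 0.03 SD per day. With c = slope × SD of timing, the spurious r is c²/(1 + c²). Rates at n = 125 use the Fisher transformation.

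| SD of timing | Spurious r | False-positive rate |
|---|---|---|
| 3 days | at most 0.008 | about 5% |
| 7 days | 0.005 to 0.042 | 5.0% to 7.5% |
| 14 days | 0.019 to 0.150 | 5.5% to 39% |

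**Question 3.** R² for f² = 0.15 is 0.15/1.15 = 0.1304. Timing noise correlated r with the emotion scores reduces it to 0.1304 × (1 − r²).

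- r = 0.2: R² = 0.1252, f² = 0.1252/0.8748 = 0.143, power at n = 119 is 0.941.
- r = 0.3: R² = 0.1187, f² = 0.1187/0.8813 = 0.135, power 0.926.
- No timing noise: power 0.951.

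**Cost of the covariate.** With days since stroke added (3 tested of 5 predictors), the required N stays 119. Power is 0.951 at 119 and 0.960 at 125, the same to three decimals as without it.

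**The case against.** The strongest objection is that this is silence, not error. A condensed article need not list every covariate; the Analysis section never says that activity limitation is the sole control, and a fuller plan may add others. That stands as a limit on severity: a reader should not infer that the sponsor has ruled time since stroke out. But the article does commit to a specific model, down to the order of entry and the visit at which activity limitation is measured, so a comment on that model is fair.

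Second, a reader might infer that timing does differ by recruitment route. The article does not say so. It describes different ways of being identified and of replying, gives no delays, and aims every route at the same target; a session could be booked to that target however the reply arrives. Only the possibility is supported.

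Third, a reader might take 8% to 21% as the expected error rate. That requires a total correlation of 0.30 to 0.45 between days since stroke and participation. The upper value means that days within a nominal one-month visit explain 0.45² = 20% of the variance in participation. Nothing in the article supports an effect of that size.

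Fourth, the main question, number 3, is barely affected. That stands.

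Finally, one might extend the covariate to question 2. No mechanism or size is shown for that: around a year after stroke, a difference of days or weeks is a small part of the elapsed time.

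**Conclusion.** The point holds as a low-severity improvement, mainly for question 1. The stated models do not adjust for recovery stage at the first visit, and the timing of that visit is fixed only loosely.

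If time correlates 0.1 to 0.3 with each score, the question 1 error rate is about 5.0% to 8.5% after activity adjustment. This assumes that the adjustment uses the one-month activity measure, that activity affects participation by 0.5, and that there is no true emotion effect. With a tight window the bias is negligible. It becomes material only if timing spreads by about two weeks or more and recovery is fast, and the article establishes neither. For question 3 the loss is one to two and a half percentage points of power. The case for acting rests on how little the remedy costs, not on a demonstrated bias.

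**What to change.** In the models for questions 1 and 3, enter days from stroke to the first assessment as a covariate beside activity limitation; for question 3 this means step 1. Where an assessment is split, count to the first sitting. Report the spread of this variable overall and by recruitment route, so that readers can see whether timing was tight. Leave the question 2 model as it is.

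The cost is one degree of freedom and a sentence in the analysis plan. No new data should be needed beyond the stroke and assessment dates, and the sample size does not change.
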